# Corindus Randomised Controlled Trial Summary

| **Title:** | Percutaneous Coronary Intervention using assisted robotic technology: a randomised controlled trial |
| --- | --- |
|  |  |
| **Short Title:** | **P**CI using **A**ssisted **R**obotic **T**echnolog**Y** trial: the **PARTY** trial |
|  |  |
| **Study Description:** | Coronary artery disease is a leading cause of death globally, nationally and locally. Currently in South Western Sydney Local Health District Interventional Cardiologists perform Percutaneous Coronary intervention (PCI) procedure which opens coronary arteries that are narrowed or blocked by the build-up of atherosclerotic plaque. PCI may also be used to relieve symptoms of coronary heart disease or to reduce heart damage during or after a heart attack.  With new technology, engineering and training development, a technology-assisted percutaneous coronary intervention (PCI) device has the potential to increase procedural accuracy, reduce radiation exposure to participants and staff, improved ergonomics, and reduce major adverse cardiac events. To date we are not aware of any randomised controlled trial data supporting this technology |
| **Study Design:** | This is a randomized controlled trial of the CorPath GRX System versus standard PCI to compare participant outcomes at 72 hours post-procedure or hospital discharge, day 30 and 1 year. |
|  |  |
| **Study Objective:** | This study will assess the safety, effectiveness including the clinical and technical performance and cost analysis of technology-assisted PCI versus standard PCI performed by a cardiologist in a randomised controlled trial. |
| **Effectiveness Performance Measures:** | **Clinical Success:**  Less than 30% residual stenosis (visual estimate) post PCI, without in-hospital major adverse coronary events (MACE).  **Technical Success:**  Defined as successful completion of the PCI absent ***unplanned*** conversion to manual operation of guidewires or balloon/stent catheter or inability to navigate vessel anatomy or poor guide catheter support. |
|  |  |
| **Safety Measures:** | **Major Adverse Cardiac Event (MACE):**  MACE that occurs within 72 hours of the procedure or prior to hospital discharge, whichever occurs first, day 30 and 1 year  **Serious Adverse Events:**  All Serious Adverse Events (SAEs) from the start of the PCI procedure until the end of the study will be summarized. |
| **Cost Measures:** | Total procedural cost of PCI at day 30 and 1 year |
| **Other Measures/Procedural Characteristics:** | **Overall Procedure Time**  Defined as the time measured from the insertion of the hemostasis sheath until the removal of the guide catheter.  **PCI Procedure Time -** Defined as the time measured from the insertion of the guide catheter until the removal of the guide catheter.  **Fluoroscopy Time –** total fluoroscopy utilized during the procedure as recorded by an Imaging System.  **Participant Radiation Exposure** – DAP (dose-area-product) and cumulative dose/air kerma as recorded during the procedure.  **Staff Radiation Exposure** – DAP (dose-area-product) and cumulative dose/air kerma as recorded during the procedure.  **Contrast Fluid Volume in mLs**  **Equipment utilization**  **Operator and staff survey of workload**  **Measurement of Lesion and Stented Segment Length**  Compare (1):   - Visual estimate of segment to be stented by clinical operator prior to delivery of PCI device(s). - CorPath GRX System measurement of the segment planned for treatment with stent. |
|  | Compare (2):   - CorPath GRX System measurement of stent length with known length of stented segment |
|  |  |
| **Participant Population:** | Participants aged 18-85 years with evidence of coronary artery disease and with a clinical indication for PCI will be asked to participate in this study. Planned recruitment of 150 participants per study arm over 3 years. |
|  |  |
| **Inclusion Criteria:** | In order to be eligible to participate in this study the individual must meet all of the following criteria:   1. Age ≥18 years- 85 years 2. Participants with coronary artery disease with clinical indication for PCI 3. Participant deemed appropriate for robotic-assisted PCI 4. Provided a signed and dated informed consent form. |
|  |  |
| **Exclusion Criteria:** | An individual who meets any of the following criteria will be excluded from participation in this study:   1. The investigator determines that the participant or the coronary anatomy is not suitable for robotic-assisted PCI. |
|  |  |
| **Investigational Sites:** | Participants will be enrolled from South Western Sydney Local health District and referred to Liverpool Hospital for the PCI procedure. |
|  |  |
|  |  |
| **Principal Investigator:** | [name], D Med Sc, FRACP FACC  Director of Medicine/Interventional Cardiologist  Liverpool Hospital, NSW Australia University of NSW, Sydney |
|  |  |
| **Device:** | **CorPath GRX System:**  Bedside Unit consists of the Extended Reach Arm, Robotic Drive and single-use Cassette.  Remote Workstation consists of the Interventional Cockpit and the Control Console. |
|  |  |
| **Indication for Use:** | The CorPath GRX is intended for use in the remote delivery and manipulation of guidewires and rapid exchange balloon/stent catheters, and remote manipulation of guide catheters during percutaneous coronary intervention (PCI) procedures. |
|  |  |
| **Manufacturer:** | Corindus Vascular Robotics  [name]  [name] |
|  |  |

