### 2.2.1 Clinical Success

Defined as less than 30% residual stenosis (visual estimate) post PCI in the lesion(s) treated, without in-hospital MACE.

MACE is defined as cardiac death, clinically relevant MI after coronary revascularization (Q-wave or non-Q-wave myocardial infarction), or clinically driven target vessel revascularization (TVR) by PCI or CABG. Clinically relevant MI after coronary revascularization will be defined by the 4^th^ Universal Definition of PCI related MI. Events as classified by the Society for Cardiovascular Angiography and Interventions definition for periprocedural MI will also be recorded for additional analysis.

The 4th Universal Definition of PCI related MI defines:

- Participants with normal baseline cardiac biomarkers
  - Cardiac troponin (cTN) >5x the 99^th^ percentile of upper reference limit (URL)
- Participants with elevated baseline cardiac biomarkers
  - Rise in post procedure cTN by >20% and be at least >5x 99^th^ percentile of URL AND
  - At least one of the following
    - New ischaemic ECG changes
    - Development of new pathological Q waves
    - Imaging evidence of new loss of viable myocardium or new regional wall motion abnormality in a pattern consistent with an ischaemic aetiology
    - Angiographic findings consistent with a procedural flow limiting complication such as coronary dissection, occlusion of a major epicardial artery or a side branch occlusion/thrombus, disruption or collateral flow or distal embolisation

The Society for Cardiovascular Angiography and Interventions definition for periprocedural MI defines:

- Participants with normal baseline cardiac biomarkers
  - CK-MB >10x upper limit normal (ULN) or cTn (I or T) >70x ULN, or
  - CK-MB >5x ULN or cTn >35x ULN plus new Q-waves in >2 contiguous leads or LBBB
- Participants with elevated baseline cardiac biomarkers
  - Baseline biomarkers are stable or falling:
    - CK-MB >10x ULN or cTn (I or T) >70x ULN of **most recent pre-procedure level**, or
    - CK-MB >5x ULN or cTn >35x ULN of **most recent pre-procedure level** plus new Q-waves in >2 contiguous leads or LBBB
  - Baseline biomarkers have not been shown to be stable or falling: CK-MB (or cTn) rises by an absolute increment equal to those recommended above plus new ST-segment elevation or depression plus signs consistent with a clinically relevant MI, such as new onset or worsening heart failure or sustained hypotension.

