## **Cost Measures**

The cost of standard PCI versus technology-assisted PCI will be measured using equipment utilisation and post procedural length of stay until discharge. The costs of these two measurements will be compared and summarized.

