# Study Design

## **Overview**

This is a randomized controlled trial of the CorPath GRX System versus standard PCI to compare participant outcomes at 72 hours post-procedure or hospital discharge, day 30 and 1 year.

The study population will consist of all consecutive participants undergoing PCI at Liverpool Hospital being asked to provide written informed consent prior to PCI and meet the eligibility criteria.

The study will randomize 300 participants equally into the 2 arms:

- Arm 1: PCI using the CorPath GRX System
- Arm 2: PCI using standard care

All enrolled participants will be followed post procedure through hospital discharge or 72 hours, whichever occurs first. The follow up will occur at day 30 and 1 year post-procedure

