## **Day only PCI patients**

Some patients will be suitable for same day discharge as their PCI procedure. In this instance, they will be asked to return the next day to the cathether laboratory clinic for a medical review as detailed in Section 7.3.

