  - Baseline biomarkers have not been shown to be stable or falling: CK-MB (or cTn) rises by an absolute increment equal to those recommended above plus new ST-segment elevation or depression plus signs consistent with a clinically relevant MI, such as new onset or worsening heart failure or sustained hypotension.

**Target Vessel Revascularization (TVR):** Ischemia-driven repeat percutaneous intervention of the target vessel or bypass surgery of the target vessel. A TVR will be considered as ischemia-driven if the target vessel diameter stenosis is
[figure not shown]
≥50% and any of the following are present:

- A positive functional study corresponding to the area served by the target vessel.
- Ischemic ECG changes at rest in a distribution consistent with the target vessel.
- Ischemic symptoms referable to the target lesion.

**In-Hospital MACE:** MACE that occurs within 72 hours of the procedure or prior to hospital discharge, whichever occurs first, in a participant treated with the CorPath GRX System.

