# Data Management, Statistical Analysis and Record Keeping

## **Statistical Methods**

This is a double-arm, open-label, randomized controlled trial of the CorPath GRX System designed to evaluate the safety and effectiveness of the clinical and technical performance of the CorPath GRX System in the delivery and manipulation of coronary guidewires and stent/balloon catheters, and remote manipulation of guide catheters for use in PCI in comparison to standard of care. The analysis of data collected as part of the RCT will include, but may not be limited to, the Objectives and Measures outlined in Section 3.0 of this protocol. Continuous variables will be summarized using the number of observations, mean, standard deviation, median, min and max values. Categorical variables will be summarized with the number and percent in each category out of the number observed. Two-sided 95% confidence intervals may be calculated and two-sided p-values < 0.05 will be considered statistically significant.

The outcome of patient radiation exposure will be analysed using variance (ANOVA). As each participant may have multiple lesions, the outcome of clinical success at day 3 will be analysed using a two level multilevel models. Logit link will be used with a binomial distribution and restricted maximum likelihood (REML) will be used for estimation. Predictor variables in the models will include treatment group.

Technical success will analysed with Fisher’s exact test, comparing the proportion of participants with technical success between the two groups. Logistic regression will be used to compare technical success accounting for lesion complexity. For all other secondary outcomes, continuous outcomes will be measured using independent t-test (or non-parametric alternative depending on distributional assumptions), and categorical outcomes analysed by Fisher’s exact test. For outcomes measured repeatedly over time, multilevel models with an appropriate link functions will be used for analysis.

All statistical analyses will be performed using SAS software (version 9.4) or other widely accepted statistical or graphical software.

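### The MACE window inside clinical success, and the early MACE measure, close at discharge, so they do not deliver the day-3 outcome the protocol says it will analyse, and time at risk depends on a post-randomisation event

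*Protocol*

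**What the plan says.** Section 2.2.1 makes clinical success a composite: "Defined as less than 30% residual stenosis (visual estimate) post PCI in the lesion(s) treated, without in-hospital MACE". The early MACE measure in the Trial Summary is "MACE that occurs within 72 hours of the procedure or prior to hospital discharge, whichever occurs first". Section 7.7.2 and Appendix A give in-hospital MACE the same window. They also word it for one arm only ("prior to hospital discharge, whichever occurs first, in a participant treated with the CorPath GRX System"), which is a separate fault, but any rewording should remove it. Section 3.1 sets the early follow-up to match: participants are "followed post procedure through hospital discharge or 72 hours, whichever occurs first".

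Two other places assume something different:

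- Section 7.4 states that "Some patients will be suitable for same day discharge as their PCI procedure" and brings these patients back the following day for the Section 7.3 review. That review lists an ECG, cardiac enzymes, adverse events and event assessment.
- Section 8.1 says that "the outcome of clinical success at day 3 will be analysed", which names a fixed time point.

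Section 2.5 compares cost through "equipment utilisation and post procedural length of stay until discharge", so time to discharge contributes to a compared outcome. Section 8.1 calls the trial open-label.

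**The concern.** A window that closes at discharge gives patients different amounts of time in which they can fail. Someone who goes home on the day of the procedure is at risk of an in-hospital MACE for a few hours. Someone who stays is at risk for up to 72 hours. Discharge happens after randomisation, in an open-label trial, and the protocol fixes no discharge criteria.

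Two things are at stake. First, early events that begin after discharge drop out of clinical success and early MACE in both arms, so neither measure describes the first three days. Second, if one arm discharges earlier, it gains apparent success without having fewer events. Clinical success is one of the two named effectiveness measures, so its definition should not move with length of stay.

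**Working it through.** **Reading the sections together.** The protocol gives no figure for this window. Its only computed design figure is the power for radiation exposure, which does not bear on the point. The core check is therefore textual.

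1. In-hospital MACE ends at the earlier of 72 h and discharge (Trial Summary, 7.7.2, Appendix A).
2. A day-only patient's window ends at discharge on the day of the procedure.
3. That patient's Section 7.3 review takes place the next day (7.4), after the window has closed.
4. A MACE with onset between discharge and 72 h is outside the window. If residual stenosis is below 30%, the patient is a clinical success. The same event at the same hour in an inpatient is a failure.
5. Section 8.1's day-3 time point is therefore not what the definition measures for anyone discharged before 72 h.

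The protocol itself describes an event that can fall in this gap. Appendix A defines subacute thrombosis as abrupt closure after the patient has left the catheterisation laboratory but within 24 h of PCI. If that happens after same-day discharge and leads to MI, target vessel revascularisation or cardiac death, clinical success does not register it.

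**Time at risk.** The discharge hour is an assumption. As a share of 72 h: 6/72 = 8%, 8/72 = 11%, 12/72 = 17%.

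**Possible size.** Let m be the true 72 h MACE risk (equal in both arms), s the share discharged the same day, and c the share of those patients' 72 h events that begin before discharge. Everyone else is taken as fully observed to 72 h. Then:

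- observed MACE = m × [1 − s × (1 − c)]
- spurious difference = m × (s₁ − s₀) × (1 − c)

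All inputs are assumed: m = 3%, 6% or 10%; c from 0.11 (flat hazard, discharge at 8 h) to 0.8 (front-loaded events).

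| True 72 h risk | Same-day 50% vs 30%: c = 0.11 | c = 0.8 | Same-day 60% vs 20%: c = 0.11 | c = 0.8 |
|---|---|---|---|---|
| 3% | 0.5 points | 0.1 | 1.1 | 0.2 |
| 6% | 1.1 | 0.2 | 2.1 | 0.5 |
| 10% | 1.8 | 0.4 | 3.6 | 0.8 |

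Example: 0.10 × (0.50 − 0.30) × (1 − 0.11) = 0.0178, or 1.8 points, which is 150 × 0.0178 = 2.7 patients per arm. At 3% risk the same gap gives 150 × 0.0053 = 0.8 of a patient at most.

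If both arms discharge 30% the same day, the difference is zero, but s × (1 − c) of all 72 h events are lost from clinical success in each arm: 0.3 × 0.2 = 6% up to 0.3 × 0.89 = 27%.

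Under a 72 h window that ignores discharge, the definition counts every 72 h event in both arms, and the difference caused by the window is zero whatever the discharge pattern.

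**The case against.** **Occurrence is not detection.** A reader might infer that any MI found at the next-day review is scored as success. The documents do not support that. The window turns on when MACE occurs, the MI definition is one of PCI-related MI, and an independent committee adjudicates from source data (Section 10.2). It could date such an MI to the procedure, before discharge. This stands: misclassification is certain only for onset after discharge. For events merely detected afterwards the text is ambiguous, because it gives no onset rule.

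**The next-day review may be meant as the day-only patient's Day 3/Discharge visit.** That is plausible, and it would explain Section 8.1's wording. But a visit schedule does not change an endpoint definition that closes at discharge, so the sections still disagree.

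**The events are not lost to the trial.** Correct. Section 2.4.1 measures MACE at every visit, and it is compared at day 30 and 1 year. The defect is confined to clinical success and early MACE.

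**Bias between arms is not shown.** Also correct. No section says that discharge timing will differ, or who decides discharge and whether they know the allocation, and participants are ideally blinded (5.3). It is a risk, not a demonstrated effect.

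**The numbers may be too small to matter.** It is tempting to take the 97.6% success rate cited in Section 1.3.2, derive 150 × 0.024 = 3.6 failures per arm, and argue that one or two moved events would change the comparison. That figure is per lesion, and failures also include residual stenosis, which discharge cannot affect. Even 4 versus 2 failures in 150 per arm gives a Fisher p-value of 0.68. The sample size rests on radiation exposure, not on this outcome.

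**Conclusion.** The inconsistency is real: the definition, the day-only pathway and the analysis section do not describe the same outcome. Post-discharge MACE within 72 h counts as success (given residual stenosis below 30%), while the same event in an inpatient counts as failure.

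The size is modest and rests wholly on assumed discharge shares, event rates and event timing. With a 20-point gap in same-day discharge, the spurious difference stays below about 2 percentage points. It exceeds 2 points only when a 40-point gap is combined with 6% to 10% risk and a nearly flat hazard. Front-loaded events shrink it, and equal discharge patterns remove it. The calculation ignores unequal next-day discharge, which could add to or offset it.

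The severity is moderate. The point does not threaten the later MACE comparisons, but an effectiveness outcome should not have a time at risk set by a post-randomisation event when a wording change avoids it.

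**What to change.** Define the MACE component of clinical success, and the early MACE measure, as MACE with onset within 72 hours of the procedure regardless of discharge, identically in both arms. State that events identified at the next-day review or the Day 30 visit count if their onset falls in that window, and give the adjudicators a rule for dating onset. Align the Trial Summary and Sections 2.2.1, 3.1, 7.7.2, 8.1 and Appendix A. Keep in-hospital MACE as a descriptive item.

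The cost is a wording amendment and an onset date collected at visits already planned. Discharge practice need not change. The success rate may come out slightly lower and be less comparable with studies that use in-hospital MACE.

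The change does not equalise detection. Section 7.3 lists cardiac enzymes, while the Section 3.3 footnote and Section 7.2.8 leave them to the investigator's discretion. Detection of biomarker-only MI will therefore still vary between patients, and those sections need to be reconciled separately.

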# Introduction

Coronary artery disease is a leading cause of death globally, nationally and locally. Currently in South Western Sydney Local Health District, Interventional Cardiologists perform Percutaneous Coronary intervention (PCI) procedure which opens coronary arteries that are narrowed or blocked by the build-up of atherosclerotic plaque. PCI may also be used to relieve symptoms of coronary heart disease or to reduce heart damage during or after a heart attack.  With new technology, engineering and training development, a technology-assisted percutaneous coronary intervention (PCI) device has the potential to increased procedural accuracy, reduce radiation exposure to participants and staff, improved ergonomics and reduce major adverse cardiac events. To date we are not aware of any randomised controlled trial data supporting this technology.

## **Device Name**

CorPath^®^ GRX System

## **Background**

Until the introduction of the CorPath^®^ 200 System into the market, all coronary interventional procedures were performed under fluoroscopic guidance with the medical team standing near the participant while maneuvering the devices manually. The interventional cardiologist and the medical team are routinely exposed to ionizing radiation [1-3]. The consequences of long-term radiation exposure, even at low doses, are meaningful and may be associated with cancer [4-12], cataracts [[3](#_ENREF_5), 13-15] and other medical problems [16, 17]. To minimize the radiation exposure, the staff is protected with heavy lead aprons and other protection devices [18 - 22]. In spite of these protective measures, the team is still exposed to radiation and therefore undergoes careful follow-up and testing for prevention of overexposure [[23](#_ENREF_24)]. While the conventional protective methods are useful to minimize radiation exposure, they create an uncomfortable working environment for the operator, who must perform precise work under a physically strenuous environment for prolonged periods of time, leading to orthopedic hazards of the profession [[24](#_ENREF_25) ,25].

CorPath is the only robotic-assisted platform cleared for percutaneous coronary intervention (PCI). Since the FDA clearance of the CorPath 200 System in 2012, operators have performed over 2000 robotic PCI procedures. Feedback indicates the System is user-friendly, offers enhanced visualization for precise stent placement and allows for a safer work environment. However, with iterative changes in technology, the CorPath 200 has been enhanced by improvements in workflow and remote guide catheter control.

The CorPath GRX System is the second generation of the CorPath platform. With CorPath GRX, workflow is streamlined by the addition of an easily positioned extended reach arm. The new arm incorporates a "touchscreen". The benefits of the touchscreen allow the tableside user to visualize the instructions. Workflow enhancements also include a redesigned cassette to allow for active guide management. The clinical improvements consist of the addition of Active Guide Management, faster guidewire rotation and improved measurement accuracy. These improvements have the potential to allow for greater robotic procedural control for the primary operator and, perhaps a reduction in not only operator but also participant and Cath Lab team radiation exposure.

One of the key differentiators between the first and second generation of CorPath is the ability to robotically manipulate the guide catheter using Active Guide Management. Using the joystick or alternatively the touchscreen, you can advance and/or rotate the guide catheter back into position.

Since all CorPath cases start with manual insertion of a guiding catheter, it is critical to have the guiding catheter seated correctly in the coronary ostium. For optimal robotic guidewire/balloon/stent delivery, adequate guide catheter support (also known as *backup support*) is necessary. Adequate guide catheter support revolves around the ability of the guide catheter to remain in position and to provide appropriate stability for the advancement of interventional equipment [26]. This guide catheter support enables the robotic procedure to progress. Sometimes, as the physician attempts to advance the guidewire or balloon/stent robotically, resistance in movement occurs causing the guide catheter to disengage from the coronary ostium. The CorPath 200 does not allow for any guide control manipulation from the remote cockpit. The physician must either leave the cockpit and adjust the guide catheter manually, or passively reengage the catheter by retracting the guidewire, to allow for proper alignment and reengagement in the coronary ostium. Having to leave the cockpit for this reason increases radiation exposure to the physician. Only after manual adjustment of the guide catheter can the CorPath case continue.

This has been addressed in the design of CorPath GRX, the next generation CorPath platform. The CorPath GRX System offers Active Guide Management which is incorporated into the re-designed cassette and radiation-shielded cockpit.

